### Multivariable Analyses

To assess the effectiveness of a prenatal omega-3 fatty acid supplementation intervention in reducing the incidence and severity of depressive symptoms during pregnancy and up to 6 weeks postpartum, a one-way analysis of variance (ANOVA) with repeated measures will be used via the MIXED procedure in SAS. A one-way ANOVA has the advantage of testing whether there are any differences between the three groups with a single probability associated with the test. The hypothesis tested is that all groups have the same mean. We will have one within factor (time) and one between factor (supplement group). The ANOVA will allow us to assess the significance of the two main effects as well as if interaction is present, adjusting for potential confounding variables. Moreover, as a repeated measures design, it will allow us to use all four BDI assessments, which in turn will provide more detailed information about the trends over time than one or two assessments would. Lastly, we will be able to look at intermediate outcomes of interest, such as the effect of the prenatal omega-3 fatty acid supplementation intervention during pregnancy, using only the three BDI assessments performed during the prenatal period in our one-way ANOVA with repeated measures model.

Women who initiate antidepressant therapy during the study period will remain in the study for its duration. However, it will be necessary to take this change in treatment into account in our multivariable analyses. Thus, in addition to the above mentioned analyses, we will also perform a subgroup analysis among those who were not taking antidepressants during the study period. We will also test whether therapy could be a confounder or effect modifier of the effect of fish oil supplementation on depressive symptomtaology over the entire study cohort.

All multivariable analyses will be performed using the MIXED procedure in SAS, as this procedure allows for missing data. While the research team will make every effort to collect data from all participants at all four time points during the study period, it is possible that a participant might miss one or two study visits. The methodological approach chosen for this proposal allows for some flexibility with the analyses performed. For example, comparisons will be drawn between baseline and 6 week postpartum BDI scores solely, as well as after taking into account the assessments drawn at 26-28 and 34-36 weeks gestation. Unlike the general linear models (GLM) procedure in SAS, the MIXED procedure does not remove all data for any subject that does not have complete data. Rather, all study participants are retained in the analysis and all available information is used.

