## Results/Outcomes

### Primary Outcome Measure

The primary outcome of interest in the proposed study is the participant's BDI score at 6 weeks postpartum. The BDI is widely accepted and will be used to measure the severity of depressive symptoms during pregnancy and in the postpartum period. It was first introduced by [name] and colleagues in 1961 (BDI-I) and consists of 21 questions about how the participant was feeling in the last week[35]. Each set of at least four possible answer choices range in increasing intensity. The questions touch on depressive symptoms such as hopelessness and irritability, cognitions such as guilt or feelings of being punished, as well as physical symptoms such as fatigue, weight loss, and lack of interest in sexual intercourse.

The test characteristics of the BDI as a depression screen among pregnant populations have been well-characterized[36,37]. In a longitudinal study among 105 pregnant women attending an urban antenatal clinic, Holcomb found the BDI to be a rapid and sensitive screening test for depression[37]. The standard cutoffs for the BDI are as follows: 0-9 for no significant depressive symptoms; 10-19 for mild to moderate depression; 20-29 for moderate to severe depression; and 30-63 for severe depression. Higher total scores indicate more severe depressive symptoms. The BDI has been used widely in clinical research and especially in pregnant populations[37-39] and has high internal consistency[40]. The questionnaire takes no more than 10 minutes to complete and is prepared at a 5^th ^to 6^th ^grade reading level.

For the proposed study, the BDI will be administered at baseline, 26-28 and 34-36 weeks gestation, and at 6 weeks postpartum. As our primary outcome of interest, depressive symptoms will be measured as a continuous variable and reported in descriptive and multivariable analyses as means and standard deviations.

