### Other Planned Exploratory Analyses

To evaluate the effect of fish oil supplementation on omega-3 fatty acid concentrations in maternal blood, we will use a mixed effect model for longitudinal data because the omega-3 fatty acid concentrations will be measured twice for each participant (at baseline and at 34-36 weeks gestation). Using this model, we can assess both the time averaged difference in the concentration between the three groups as well as the change in the concentration over the two measurement times between the three groups. To evaluate the effect of fish oil supplementation on the proinflammatory cytokines referenced, we will use a mixed effect model for longitudinal data because each proinflammatory cytokine level will be measured twice for each participant (at baseline and at 34-36 weeks gestation). Using this model, we can assess both the time averaged difference in the levels between the three groups as well as the change in concentration over the two measurement times between the three groups. To evaluate the effect of fish oil supplementation on standard obstetrical outcomes including but not limited to length of gestation, birth weight, Apgar score, mode of delivery, blood loss at delivery, and preeclampsia, we will use multiple regression for continuous outcomes variables and logistic regression for dichotomous outcome variables, and in either of these approaches, an indicator for fish oil supplementation will be the primary independent variable.

The exploratory aims are intended to generate preliminary data elucidating the possible mechanism of action of fish oil supplementation in the prevention of depression in pregnancy and the postpartum period. In particular, the role of fish oil in inhibiting production of proinflammatory cytokines may provide an explanation for the observed link between depression in pregnancy and preterm birth, a condition known to be associated with inflammation. Although we will be unable to definitively explore these relationships in the proposed study, we intend for these aspects of the study design to generate preliminary data which will allow us to refine our dosing, expected effect sizes, and hypotheses for a larger, multicenter study of the effectiveness of fish oil in prevention of major depression in pregnancy and postpartum.

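### No primary test is designated, and the repeated-measures hypothesis, read as the group main effect, matches neither the 6-week BDI outcome nor the power calculated for it

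*Protocol article*

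**What the plan says.** Under Primary Outcome Measure the article states: "The primary outcome of interest in the proposed study is the participant's BDI score at 6 weeks postpartum". The same section gives the schedule: "the BDI will be administered at baseline, 26-28 and 34-36 weeks gestation, and at 6 weeks postpartum". Sample Size Considerations powers a three-group one-way ANOVA for a halving of the mean BDI at that one postpartum visit.

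Multivariable Analyses describes a different model: repeated measures in SAS MIXED, with supplement group as the between factor and time as the within factor. It presents a single overall test ("The hypothesis tested is that all groups have the same mean"), says that both main effects and their interaction will be assessed, and gives as an advantage that "it will allow us to use all four BDI assessments, which in turn will provide more detailed information about the trends over time". An antenatal version is to be fitted "using only the three BDI assessments performed during the prenatal period". Later in the section, as an illustration of flexibility, "comparisons will be drawn between baseline and 6 week postpartum BDI scores solely", and also with the two intermediate visits taken into account.

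For fatty acids, Other Planned Exploratory Analyses says "we can assess both the time averaged difference in the concentration between the three groups", together with the change between the two measurements. The cytokines are handled in the same way.

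**The concern.** In a model with group and time as factors, the one test of equal group means is the group main effect, which averages each arm over its visits. Here one of the four visits is baseline. Under Study Visits, the baseline BDI is taken at the visit where the first supply of supplement is handed out, so the arms can differ there only by chance. The main effect is therefore a different quantity from "BDI score at 6 weeks postpartum", and the 80% power computed for the 6-week visit does not carry over to it.

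The other planned analyses do not settle the matter. The interaction has 6 degrees of freedom and responds to any departure from parallel profiles, so it does not isolate 6 weeks. The baseline versus 6-week comparison does concern the right visit, but it is offered as an example and its form is not stated. With no test ranked first, the trial's main result could be a diluted average, or could be picked from several results after the data are seen.

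**Working it through.** **Inputs from Sample Size Considerations.** Control mean 8.4, SD 6.4, a 50% reduction in either active arm (8.4 × 0.5 = 4.2 points), alpha 0.05, 35 women per arm.

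**Assumptions not in the article.** SD 6.4 at every visit; the same correlation ρ between any two visits, taken as 0.3, 0.5 and 0.7; complete data at 35 per arm; and two time courses for the effect at baseline, 26-28 weeks, 34-36 weeks and 6 weeks postpartum: early (0, 1, 1, 1) and linear (0, 1/3, 2/3, 1).

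**Step 1: the plan's own figure.** Means of 8.4, 4.2 and 4.2 have variance (2/9) × 4.2² = 3.920, and 3.920 / 6.4² = 3.920 / 40.96 = 0.0957. The noncentrality is 105 × 0.0957 = 10.05. With 2 and 102 df, power is 80.5% at 35 per arm and 79.3% at 34. The stated 35 per arm is reproduced, for a test at 6 weeks alone.

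**Step 2: what the group main effect estimates.** The four-visit average of the effect is:
- early: 4.2 × (0+1+1+1)/4 = 3.15 points
- linear: 4.2 × (0+1/3+2/3+1)/4 = 2.10 points

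**Step 3: power of the group main effect.** The variance of a woman's four-visit mean is 40.96 × (1+3ρ)/4, which is 19.46, 25.60 and 31.74 for ρ = 0.3, 0.5 and 0.7. The noncentrality is 105 × 3.920 × (average profile)² / variance. At ρ = 0.5 this is 105 × 3.920 × 0.5625 / 25.60 = 9.04 (early) and 105 × 3.920 × 0.25 / 25.60 = 4.02 (linear).

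**Step 4: the alternatives.** For a 6-week test with baseline as covariate, the residual variance is 40.96 × (1−ρ²), or 30.72 at ρ = 0.5, giving noncentrality 105 × 3.920 / 30.72 = 13.40. (The one degree of freedom spent on the covariate is ignored.) For change from baseline to 6 weeks, the variance is 2 × 40.96 × (1−ρ). The interaction is an F test with 6 and 9 × 34 = 306 df.

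| Test, 35 per arm | ρ = 0.3 | ρ = 0.5 | ρ = 0.7 |
|---|---|---|---|
| 6 weeks, unadjusted (as sized) | 80.5% | 80.5% | 80.5% |
| Group main effect, early | 87% | 76% | 66% |
| Group main effect, linear | 52% | 41% | 34% |
| Interaction, early | 67% | 84% | 98% |
| Interaction, linear | 52% | 69% | 92% |
| Change, baseline to 6 weeks | 65% | 81% | 96% |
| 6 weeks, baseline as covariate | 84% | 91% | 98% |

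**Step 5: when does averaging cost power?** The main effect and the unadjusted 6-week test have equal power when 4 × (average profile)² = 1 + 3ρ. For the early profile this gives ρ = (4 × 0.5625 − 1)/3 = 0.42, and below that value the average is the more powerful test. For the linear profile the break-even is ρ = 0, so averaging loses power at every positive correlation.

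**Step 6: the related models.** With baseline as one of three responses, the antenatal main effect is at most 2/3 of a full effect. With baseline as one of two responses, the time-averaged biomarker difference is in expectation half the difference at 34-36 weeks. The biomarker change, also planned, is not diluted.

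**The case against.** A reader might infer that the plan never tests its primary outcome. The text does not support that. The sentence on equal means can be read as a general description of ANOVA; the interaction is planned too; the baseline versus 6-week comparison addresses the right visit; and the group-by-time model contains the 6-week contrast, which needs only to be named. All of this stands, and it limits the finding to an undesignated primary test plus a mismatch under one natural reading. It does not reduce the finding to detail that an analysis plan would supply: the article itself states the model, the responses and the hypothesis, and these do not line up with its own outcome and sample size.

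A reader might also infer that power always falls, or quote the extreme case of an effect seen only postpartum (1.05 points, 13% power at ρ = 0.5). Step 5 refutes the first inference. The second uses the time course that the article supports least, because the Aims expect antenatal benefit as well. An early effect fits that expectation better, and its loss at ρ = 0.5 is modest: 76% against 80.5%.

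Nor are the antenatal visits irrelevant, since BDI at 26-28 and 34-36 weeks is a named secondary outcome. Only baseline carries no treatment effect. The biomarker point is minor: those analyses are exploratory, and the undiluted change is already planned.

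**Conclusion.** The concern holds in this form. The article fixes a 6-week outcome and powers a 6-week test, then plans a main effect, an interaction and a baseline versus 6-week comparison without saying which one decides the trial. If the stated hypothesis is taken as the group main effect, the estimate falls to 75% (early) or 50% (linear) of the 6-week effect. Power then lies between 34% and 87%, depending on time course and correlation, instead of the planned 80%. That some dilution occurs follows from randomization and from counting baseline as a response, for any effect that is no larger at the antenatal visits than at 6 weeks. The amount of dilution rests on the assumed time courses, and the power figures also on the assumed correlations, equal SDs and common correlation between visits. None of these is given in the article. The point should be settled before analysis because it determines what the primary result is.

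**What to change.** In Multivariable Analyses, declare one primary test: equality of the three arms at 6 weeks postpartum, estimated from the mixed model. Use BDI at 26-28 weeks, 34-36 weeks and 6 weeks as responses, with arm, visit, arm-by-visit, baseline BDI and baseline-by-visit as terms. Keeping baseline as a response with its mean constrained equal across arms is an acceptable alternative; leaving it as a free response is not. With complete data and an unstructured covariance, the 6-week contrast from this model is the baseline-adjusted comparison in the last row of the table.

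Make the overall group effect, the interaction, the time trends and the other baseline versus 6-week comparisons secondary. Treat baseline in the same way in the antenatal model. For fatty acids and cytokines, rely on the change already planned or on the baseline-adjusted 34-36-week value, and drop the time-averaged difference as a measure of effect.

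The cost is a few sentences of plan text. The data, the sample size and the SAS procedure stay the same.

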## Methods

### Aims

The aim of this study is to determine whether EPA or DHA will prevent pregnancy-related depressive symptoms. We hypothesize that EPA-rich fish oil supplementation and DHA-rich fish oil supplementation will reduce the risk of antenatal and postpartum depressive symptoms in women who are at elevated risk for depression based on a previous history of major depressive disorder, a previous history of postpartum depression, or an Edinburgh Postnatal Depression Scale (EPDS) score between 9 and 19 in early pregnancy. The study will also directly compare the effects of EPA and DHA on depressive symptoms as measured by the Beck Depression Inventory score. In addition we hypothesize that fewer pregnant women assigned to the fish oil supplementation will require treatment with antidepressant medications and if medicated, a lower total dose will be required than for women receiving placebo. We will recruit pregnant women who are between 12-20 weeks gestation and will follow them through their pregnancies and up to 6 weeks postpartum. The women participating in this study will be receiving prenatal care at two health systems in southeastern Michigan, the University of Michigan Hospitals and Clinics and St. Joseph Mercy Health System/Integrated Health Associates. These health systems are located in Ann Arbor, Michigan and Ypsilanti, Michigan and the surrounding communities.

This study also has three secondary aims that will generate preliminary data on possible mechanisms of action of EPA and DHA in mental health. First, we will examine the relationship between EPA and DHA, maternal plasma fatty acid levels, and symptoms of depression. Second, we will explore whether EPA and DHA reduce depressive symptoms by reducing synthesis of pro-inflammatory cytokines IL-6, IL-1β, and TNF-α. Third, we will examine the relationship between EPA and DHA and standard pregnancy outcomes, including birth weight and length of gestation.

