### Sample Size Considerations

We hypothesize that (i) fish oil supplementation will reduce the severity of depressive symptoms in the postpartum period among women at risk and that the (ii) EPA-rich fish oil (intervention #1) and DHA-rich fish oil (intervention #2) will be equally efficacious in reducing depressive symptoms. Our sample size calculation is based on the premise that fish oil supplementation of either the EPA-rich or DHA-rich dose will result in a 50 percent reduction in the mean BDI score at 6 weeks postpartum. Sample size calculations were generated in *nQuery Advisor *Version 6.01 based on data from a previous study conducted among the target population by one of the co-investigators, [name]. In that observational study, she observed a mean BDI score of 8.4 with a standard deviation of 6.4 among postpartum mothers at risk for depression. Assuming a significance level of 0.05, a one-way analysis of variance test, a variance of means (variance of the individual group means) of 3.920, a standard deviation of 6.4, and an effect size (the index of the separation expected among the observed means) of 0.0957, we will need to recruit 105 pregnant women (35 pregnant women in each of the three groups) to have 80% power to detect at least one group difference in the mean BDI score. We propose to recruit 126 pregnant women to account for the possibility of up to 10% study dropout and 10% initiating antidepressant therapy during the study period (to provide sufficient numbers for subgroup analyses).

Our decision to hypothesize a 50% reduction in the mean BDI score between intervention and control groups is based on results from published studies. Freeman and colleagues recently conducted two clinical trials[41,42] of omega-3 fatty acid supplementation and perinatal depression, using the EPDS as their primary measure of depressive symptomatology and reported a 51% and 41% reduction in EPDS score over an 8 week study period. A comparable study in a non-pregnant population demonstrated a similar effect size[43].

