### Covariate Assessment

Other experiences of the participant that might influence depressive symptomatology must be considered as potential confounders. These include other exposures that occur during the prenatal and postpartum period. In addition to detailed information on the intervention and outcomes of interest, we will collect a detailed demographic, behavioral, dietary, and medical history from each participant at the time of study enrollment and review the participant's medical record and document any complications incurred during pregnancy.

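### The covariate rules let antidepressant start and other post-randomisation exposures be treated as confounders and kept in the final model, which can bias the randomised comparison

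*Protocol article*

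**What the plan says.** All of this is in the protocol article.

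- **Participants/Eligibility Criteria** excludes women on antidepressants, so use on study starts after enrolment.
- **Aims** hypothesises that "fewer pregnant women assigned to the fish oil supplementation will require treatment with antidepressant medications". **Secondary Outcomes** lists the need for depression-related treatment and antidepressants as item (a).
- **Study Visits** refers any woman with a BDI of 20 or more, or with MDD on the MINI, to a provider who may prescribe an antidepressant. The BDI is also the primary outcome instrument.
- **Multivariable Analyses** says the change in treatment must be taken into account and plans two things. One is a restriction: "we will also perform a subgroup analysis among those who were not taking antidepressants during the study period". The other covers the whole cohort: "We will also test whether therapy could be a confounder or effect modifier of the effect of fish oil supplementation".
- **Covariate Assessment** says of potential confounders: "These include other exposures that occur during the prenatal and postpartum period". It also has pregnancy complications documented.
- **Descriptive Analyses** controls for possible confounders in all analyses and retains covariates that shift the coefficient of interest by more than 10%. The same paragraph puts all analyses on an intent-to-treat basis. The main repeated-measures model is then described as adjusted for potential confounders.

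**The concern.** A confounder of a randomised treatment has to precede it. By the plan's own account, antidepressant start follows randomisation, responds to the woman's depressive symptoms and is expected to differ by arm. Conditioning on it compares women who are no longer alike by randomisation: a placebo woman who did not start and a fish-oil woman who did not start have been selected to different degrees.

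Nothing in the three analysis sections limits candidate covariates to those measured before randomisation. The retention rule makes this worse. A change-in-estimate rule, applied to a consequence of treatment or of outcome severity, tends to keep the variable because it absorbs part of the difference between arms. The adjusted model would then estimate something other than the intent-to-treat effect, and the trial is sized with only 80% power for the full 4.2 points.

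**Working it through.** **Inputs from the document (Sample Size Considerations).** "a mean BDI score of 8.4 with a standard deviation of 6.4 among postpartum mothers at risk for depression"; a 50% reduction in either active arm, giving means 8.4, 4.2 and 4.2; three equal arms; 10% expected to start an antidepressant.

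**The plan's own figure first.** Variance of means = [(8.4 − 5.6)² + 2(4.2 − 5.6)²]/3 = 3.92. Effect size = 3.92/6.4² = 0.0957. The noncentral F test with df 2 and 3n − 3, noncentrality 3n × 0.0957 and alpha 0.05 gives 80.5% power at n = 35 and 79.3% at n = 34. So 35 per group (105) is reproduced, and the true difference to work with is 4.2.

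**Assumptions not in the document.** Earlier severity is normal with the same means and SD. A woman starts when it reaches a threshold c. Its correlation r with the 6-week BDI is 0.5 or 0.7. An antidepressant lowers the 6-week BDI by d points, at first d = 0. The two active arms are pooled.

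**Step 1, threshold.** Solving [P(Z > (c − 8.4)/6.4) + 2P(Z > (c − 4.2)/6.4)]/3 = 0.10 gives c = 14.2. Then 18.2% of placebo and 5.9% of fish-oil women start; check: (18.2 + 2 × 5.9)/3 = 10.0.

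**Step 2, antidepressant-free subset.** With h = (c − m)/6.4, the non-starter mean is m − r × 6.4 × φ(h)/Φ(h). For r = 0.5:
- placebo: 8.4 − 0.5 × 6.4 × 0.2643/0.8179 = 7.37
- fish oil: 4.2 − 0.5 × 6.4 × 0.1175/0.9410 = 3.80
- difference 3.57

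For r = 0.7 the means are 6.95 and 3.64, difference 3.31.

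**Step 3, adjustment for starting.** The coefficient averages the non-starter and starter differences with weights n₀n₁/(n₀ + n₁), here 0.190 and 0.0239. The starter differences, from m + r × 6.4 × φ(h)/(1 − Φ(h)), are 2.47 (r = 0.5) and 1.77 (r = 0.7).
- r = 0.5: (0.190 × 3.57 + 0.0239 × 2.47)/0.2139 = 3.44
- r = 0.7: (0.190 × 3.31 + 0.0239 × 1.77)/0.2139 = 3.14

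**Step 4, what changes the answer.** A constant drug effect leaves the subset and adjusted values unchanged, but the full-cohort contrast becomes 4.2 − d × (0.182 − 0.059). If instead c = 20, the BDI referral score, 3.5% and 0.7% start.

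| Scenario | Full cohort | Subset, r 0.5 / 0.7 | Adjusted, r 0.5 / 0.7 |
|---|---|---|---|
| c = 14.2, d = 0 | 4.20 | 3.57 / 3.31 | 3.44 / 3.14 |
| c = 14.2, d = 4 | 3.71 | 3.57 / 3.31 | 3.44 / 3.14 |
| c = 14.2, d = 8 | 3.22 | 3.57 / 3.31 | 3.44 / 3.14 |
| c = 20, d = 0 | 4.20 | 4.00 / 3.93 | 3.98 / 3.89 |

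In the first row the shortfall is 15% and 21% (subset), 18% and 25% (adjusted). In the last row it runs from 4.6% to 7.3%.

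**Step 5, would the 10% rule keep therapy?** In 5,000 simulated trials with 38 women per arm (126 × 0.9/3), at c = 14.2 and d = 0, it did so in about 76% (r = 0.5) and 88% (r = 0.7). With d = 4 this fell to about 32% and 67%. With c = 20 and d = 0 it was roughly a fifth to a third.

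**The case against.** The strongest reply is that the full-cohort analysis is not displaced. The antidepressant-free analysis is announced as additional, starters stay in the study, and the section on missing data keeps every participant in the mixed model. That stands: a reader might infer from the subgroup sentence that starters are dropped from the main analysis, and the text does not say so. For the subset the issue is labelling and interpretation.

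Therapy is also only to be tested as a confounder or effect modifier; it reaches the final model through the 10% rule, and testing effect modification is not itself adjustment. That also stands, but the rule is stated for all analyses and has no exemption for variables arising after randomisation.

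Four stronger readings are tempting and not supported:

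- **That the bias always runs towards zero.** With r = 0.5 and an 8-point drug effect, the full-cohort contrast (3.22) is nearer zero than both the subset (3.57) and the adjusted value (3.44).
- **That adjustment blocks part of the treatment effect.** With d = 0 nothing passes through the drug; the shrinkage arises because starting marks prognosis.
- **That treatment is hypothesised to change every prenatal and postpartum exposure.** The Aims say this explicitly only for antidepressants. Complications are to be documented, and the text does not say that they enter the models. Gestational hypertension, gestational diabetes and preeclampsia are, however, listed secondary outcomes.
- **That dose will be compared only among medicated women.** The Aims state a hypothesis ("if medicated, a lower total dose will be required"), but no such analysis is described, and a condensed article may leave it elsewhere.

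**Conclusion.** The point holds as a fault in stated rules. Taken together, Covariate Assessment, Descriptive Analyses and Multivariable Analyses allow consequences of treatment or of outcome severity to be handled as confounders and retained in a model that is called intent to treat. This follows from the text and needs no simulation.

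The size does not follow from the text. Losing 15 to 25% of a 4.2-point difference requires 10% starting overall, selection by earlier severity with correlation 0.5 to 0.7, and no drug effect. If starting requires a BDI of 20 or more, the loss is about 5 to 7%. That is a low-end case, since MDD on the MINI also triggers referral and the implied overall start rate, (3.5 + 2 × 0.7)/3 = 1.6%, is well below the plan's 10%. With a sizeable drug effect, the distance and even the order between the full-cohort and conditioned estimates change. The defensible statement is that the conditioned estimates can be biased, by an amount and in a direction relative to the full-cohort contrast that the plan cannot know in advance. The sample size is unaffected.

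**What to change.** 1. Limit adjustment in every treatment comparison to pre-specified covariates measured before randomisation, and do not apply the 10% rule to any variable arising later.
2. State that the analysis of all randomised women, regardless of antidepressant start, is the basis for conclusions.
3. Report antidepressant start and pregnancy complications by arm as outcomes.
4. Label the antidepressant-free subset and any therapy-adjusted or effect-modification model as exploratory, non-randomised comparisons. Alternatively, replace them with a mixed model over all randomised women in which BDI values after antidepressant start are set to missing.

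The cost is a change of wording and, for the alternative in item 4, one further model run. No new data or participants are needed. The downside of that alternative is its missing-at-random assumption: given the recorded BDI values and covariates, starters' unobserved antidepressant-free scores are taken to behave like those of comparable non-starters. The plan would have to state this.

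### The analysis section does not say which BDI analysis decides the 6-week primary outcome, and does not carry forward the single ANOVA that was sized

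*Protocol article*

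**What the plan says.** - **Outcome.** Primary Outcome Measure: "The primary outcome of interest in the proposed study is the participant's BDI score at 6 weeks postpartum". Secondary Outcomes lists BDI at the two later prenatal visits as secondary.
- **Sizing.** Sample Size Considerations: "Assuming a significance level of 0.05, a one-way analysis of variance test", giving 35 women per group and 105 in all. The inputs are that "she observed a mean BDI score of 8.4 with a standard deviation of 6.4 among postpartum mothers at risk for depression" and that either fish oil "will result in a 50 percent reduction in the mean BDI score at 6 weeks postpartum".
- **Model.** Multivariable Analyses assesses effectiveness over pregnancy and up to 6 weeks postpartum with a repeated-measures ANOVA in SAS MIXED, using all four BDI scores. It commends ANOVA for yielding one probability, then adds: "The ANOVA will allow us to assess the significance of the two main effects as well as if interaction is present".
- **Prenatal model.** The same section describes a further model, "using only the three BDI assessments performed during the prenatal period in our one-way ANOVA with repeated measures model", and calls this a look at intermediate outcomes.
- **Two-visit comparison.** Later in the section the approach is described as leaving some flexibility, and "comparisons will be drawn between baseline and 6 week postpartum BDI scores solely, as well as after taking into account the assessments drawn at 26-28" weeks (likewise for the 34-36 week visit).

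Nothing in the article says which model, or which term of a model, decides the primary outcome.

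**The concern.** The plan fixes one outcome, one time point and one sized test, but the analysis section does not contain that test. In its place stand three results that bear on the supplement: the four-visit group effect, the four-visit group-by-time interaction and the baseline-to-6-week comparison. They answer different questions. The group effect is a difference averaged over all visits, the interaction is any difference in trajectory, and the two-visit comparison is the change to 6 weeks. The Aims hypothesis, that fish oil "will reduce the risk of antenatal and postpartum depressive symptoms in women who are at elevated risk for depression", is broad enough for any of them to be cited in support.

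Two things are at stake. If the choice is made after the results are seen, 0.05 is no longer the error rate of the conclusion. And if the four-visit group effect is taken as the answer, the power statement does not apply to it, because that effect includes a baseline score that treatment cannot affect and prenatal scores for which no effect was assumed.

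**Working it through.** **1. The plan's own figure.** Means 8.4, 4.2 and 4.2 have grand mean 5.6. Variance of means = (2.8² + 1.4² + 1.4²)/3 = 11.76/3 = 3.920. Index = 3.920/6.4² = 3.920/40.96 = 0.0957. With 35 per group the noncentrality is 105 × 0.0957 = 10.05 on 2 and 102 df, and power at 0.05 is 80.5%; 34 per group gives 79.3%. The stated 35 per group is reproduced. It belongs to the one-way ANOVA of the 6-week score alone.

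**2. False-positive rate if more than one result may count.** Assumptions not in the article: any p < 0.05 counts as success; four normal BDI scores with equal correlation 0.3, 0.5 or 0.7; complete data; 35 per group; no treatment effect. There were 40,000 simulated trials per setting. The two-visit comparison is the F test on the change from baseline to 6 weeks.

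| Results allowed to count | r = 0.3 | r = 0.5 | r = 0.7 |
|---|---|---|---|
| 6-week ANOVA alone | 5.0% | 4.8% | 5.0% |
| Two-visit comparison or four-visit interaction | 8.3% | 8.1% | 8.2% |
| Four-visit group effect or interaction | 9.7% | 9.5% | 9.9% |
| All three | 12.9% | 12.6% | 12.9% |

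Running the two-visit comparison as a baseline-adjusted analysis gives 8.7%, 8.4% and 8.7% in the second row and 12.7%, 12.5% and 13.0% in the last. The assumed correlation hardly matters.

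**3. Power of the four-visit group effect under the planning effect.** The variance of a woman's four-visit mean is 40.96 × (1 + 3r)/4, which is 25.6 at r = 0.5. The effect on that mean is 4.2 points times the average share of the effect over the four visits, with baseline at zero. With two active arms alike, the variance of means is (2/9) × effect².

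| Onset of the effect | Effect on four-visit mean | Variance of means | Index at r = 0.5 | Noncentrality (× 105) | Power |
|---|---|---|---|---|---|
| Full at every follow-up visit | 4.2 × 3/4 = 3.15 | 2.205 | 0.0861 | 9.04 | 76% |
| Gradual (1/3, 2/3, 1) | 4.2 × 2/4 = 2.10 | 0.980 | 0.0383 | 4.02 | 41% |
| Only at 6 weeks | 4.2 × 1/4 = 1.05 | 0.245 | 0.0096 | 1.01 | 13% |

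Simulation gives 76%, 42% and 13%. The same formula gives 87%, 52% and 16% at r = 0.3, and 66%, 34% and 11% at r = 0.7. So a full early effect with weakly correlated visits would keep power above 80%, but the gradual and late cases fall well short at every correlation tried.

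**4. Power of the proposed deciding test.** Adjusting the 6-week score for baseline leaves variance 40.96 × (1 − r²), which is 30.72 at r = 0.5. The index is 3.920/30.72 = 0.1276 and power is about 91% with 35 per group (84% at r = 0.3, 98% at r = 0.7). This approximates the MIXED contrast when data are complete.

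**The case against.** The best defence is that the plan is less open than it looks. The outcome and time point are fixed. The prenatal scores are already listed as secondary, and the prenatal-only model is introduced as an intermediate look. The group effect and interaction are ordinary terms of one model. The two-visit sentence stands in a paragraph on missed visits, so it can be read as a supportive analysis. A separate analysis plan may also name the deciding term.

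Much of this stands, and it limits the point in four ways.

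- A reader might infer that the trial's false-positive rate is 13-16%. The article does not support that as a property of the plan. It needs a rule that any significant result counts, which is nowhere stated. The upper end (15-16%) also needs the prenatal-only tests, which the article already places below the primary outcome.
- A reader might infer that each analysis is to be tested at the full 0.05. That level appears only in the sample-size paragraph. The article neither assigns it to each BDI analysis nor mentions an adjustment.
- A reader might point to how often the four-visit group effect and the two-visit comparison reach opposite verdicts under the planning effect (about 35%, 58% and 72% of simulated trials for full, gradual and late onset). Most of that reflects dilution of the group effect. Against the four-visit interaction, the two-visit comparison disagrees in only about 15-17%.
- Naming any one test would cure the multiplicity. The choice of the 6-week contrast rests on its match with the named outcome and the sizing.

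The defence does not remove the core. The article is not merely silent: it sets out several analyses of the primary scale, offers the choice among them as an advantage, and omits the one it sized.

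**Conclusion.** The point holds in a limited form. The article names and sizes one test of 6-week BDI, then plans other analyses of the same scale without saying which decides.

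The size of the problem is conditional. If any of the planned results could carry the claim at 0.05, the false-positive rate would be about 8-9% for the two-visit comparison with the four-visit interaction, and about 13% with the four-visit group effect added, against 5% for one named test. These figures assume visit correlations of 0.3-0.7, complete data and normal scores.

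Separately, and without any assumption about how significant results would be used, the stated 80% power does not describe the four-visit group effect. At correlation 0.5 that power is about 76%, 41% or 13%, depending on when the effect appears. The onset patterns and the correlation are assumptions, since the article gives neither.

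**What to change.** In Multivariable Analyses, name one deciding test: the three-group (2 df) contrast of BDI at 6 weeks postpartum from the MIXED model, adjusted for baseline BDI, at 0.05. Then state the standing of the rest:

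- the baseline-versus-6-week comparison is a sensitivity analysis;
- the overall four-visit group effect and the group-by-time interaction are secondary or supportive;
- the prenatal-only model stays secondary, as Secondary Outcomes and the description of it as intermediate already imply.

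The cost is wording only. No women, visits or data are added, every planned model can still be run, and by step 4 of the working the sample size remains sufficient for the named test under the planning assumptions. The small downside is that a significant result from one of the other analyses can no longer carry the efficacy claim on its own.
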